### **5.3.4      Safety laboratory (routine biochemistry and hematology, coagulation, urinalysis, complement activation, inflammatory and immune response)**

#### **5.3.4.1      Routine biochemistry and hematology**

Routine biochemistry and hematology will be performed at visit 1, visit 1a, visit 2 prior to the first injection, visit 3, visit 4, visit 5, visit 6, visit 7, visit 9 and visit 12.

The parameters to be assessed for routine biochemistry and hematology are described in Appendix 3. There is no food restriction prior to blood sampling. The samples will be collected and processed according to standard hospital procedures and assessed by the local laboratory of the participating sites.

Special attention is required for the liver related enzymes in the clinical biochemistry assessments. A number of these liver enzymes (ASAT, ALAT and LDH) are also present in muscle and hence elevated levels are found in plasma (or serum) upon muscle damage, as in DMD patients. Indeed, these ASAT and ALAT findings in DMD patients have been found to correlate quantitatively with muscle specific CK levels in plasma (or serum) in DMD patients. Therefore, changes in ASAT and ALAT should be monitored in relation to CK for the evaluation of hepatotoxicity. If the changes in ASAT and ALAT levels (of over 3xULN) is disproportional to the CK changes, further evaluation is required. Dependent on the findings, this can include (i) further data analysis (e.g. graphical evaluation of trends in ALAT, ASAT and CK over time and compared to pre-treatment levels and/or regression analysis between ALAT/ASAT and CK levels for all samples of the patient), (ii) taking an additional confirmatory sample, (iii) starting more frequent monitoring and/or (iv) evaluating other alternative explanations. The sponsor should be notified of such concern. If deemed necessary, drug administration will be discontinued.

Other measures of hepatic and biliary function, including bilirubin,  $\gamma$ GT and ALP are not affected by the disease. However, ALP may be influenced by age (ALP from bone).

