### **5.6.5 Safety laboratory**

### **5.6.5.1      Routine biochemistry and hematology**

Routine biochemistry and hematology will be performed at selected visits, refer to Tables 6 - 14 in Appendix 2 for the exact time points.

The parameters to be assessed for routine biochemistry and hematology are described in Appendix 3. There is no food restriction prior to blood sampling. The samples will be collected and processed according to standard hospital procedures and assessed by the local laboratory of the participating sites.

Non-clinical studies with PRO051 suggest that it potentially may have hepatotoxic and nephrotoxic properties as it accumulates in the liver and kidney and is also associated with thrombocytopenia.

Therefore, monitoring of hepatic and renal function as well as thrombocyte count is of paramount importance. However, standard markers of hepatic and renal function may be confounded by the effects of DMD e.g. DMD subjects may have elevated ALAT, ASAT and CK levels (common markers of hepatic function) due to 'leaky' sarcolemmal membranes around muscle fibers, and serum and urinary creatinine concentrations (markers of renal function) may be variable due to changes in muscle mass. With this information in mind, the following parameters will be used for monitoring hepatic and renal function:

Hepatic function:      ALAT, ASAT, ALP, total bilirubin, bilirubin fractions (direct bilirubin),  $\gamma$ -GT, GLDH and LDH.

Renal function:      Urinalysis (including microscopy), serum and urine cystatin C, KIM-1, alpha-1-microglobulin and serum creatinine.

Urinalysis will be conducted on the first morning specimen after 8 hours of not drinking.

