#### **8.5.5.4      Safety analysis**

- Adverse events (AEs) will be coded and presented using MedDRA. The overall incidence, the incidence of possibly or probably related as well as the incidence of serious adverse events will be summarized per body system in tables. An adverse event that occurred during the study medication period or at follow-up will only be counted as an adverse event if it was either not present at baseline or it was present at baseline but increased in severity during the treatment period.
- Vital Signs (supine blood pressure and heart rate): Descriptive statistics (n, mean, standard deviation, median, minimum, and maximum) will be provided on blood pressure along with heart rate at baseline and all post-dose assessments.
- Hematology, urinalysis and clinical chemistry parameters: Descriptive statistics (n, mean, standard deviation, median, minimum, and maximum) will be provided on values at baseline and all post-dose assessments. Descriptive statistics will be calculated on the change from baseline measurements. Out-of-normal-range values will be indicated for each parameter. The change in out-of-normal-range values after administration and at follow up versus baseline will be summarized by means of shift-tables.
- ECG: Descriptive statistics (frequency, mean, standard deviation, median, minimum, and maximum) on ECG parameters will be provided at baseline and all post-baseline

assessments. Changes from baseline measurements will be calculated and descriptive statistics will be computed. Shift tables will also be provided to indicate changes in ECG parameters over time.

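### The planned ASAT, ALAT and LDH summaries (unadjusted change, normal-range shift tables) do not follow the protocol's own rule that ASAT and ALAT be read against CK

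*Protocol*

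**What the plan says.** Protocol 8.5.5.4 (Safety analysis) gives hematology, urinalysis and clinical chemistry one common treatment: descriptive statistics at baseline and at every post-dose assessment, flags for values outside the normal range, and two comparative summaries. The first is change: "Descriptive statistics will be calculated on the change from baseline measurements". The second is categorical: "The change in out-of-normal-range values after administration and at follow up versus baseline will be summarized by means of shift-tables". No parameter is treated differently, and CK is not mentioned as a reference for any other enzyme.

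Section 5.3.4.1 says ASAT, ALAT and LDH are also present in muscle, "hence elevated levels are found in plasma (or serum) upon muscle damage, as in DMD patients". It adds that ASAT and ALAT correlate quantitatively with CK in these patients, and concludes: "Therefore, changes in ASAT and ALAT should be monitored in relation to CK for the evaluation of hepatotoxicity". The CK rule names ASAT and ALAT; LDH is named only as a muscle-derived enzyme.

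For the extension, 5.6.5.1 says "Non-clinical studies with PRO051 suggest that it potentially may have hepatotoxic and nephrotoxic properties", calls hepatic and renal monitoring highly important, and repeats the warning in softer terms: "DMD subjects may have elevated ALAT, ASAT and CK levels (common markers of hepatic function").

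The only CK-relative analysis the protocol describes is for the individual patient. Under 5.3.4.1, ASAT or ALAT changes (over 3 x ULN) that are out of proportion to CK require further evaluation, which may include trend plots or "regression analysis between ALAT/ASAT and CK levels for all samples of the patient".

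**The concern.** The protocol states how ASAT and ALAT must be read if they are to say anything about the liver, then fixes a group summary that reads them another way. Two things follow.

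First, a normal-range shift table registers only crossings of the range limit. A boy who starts well above that limit because of his muscle disease has nothing left to cross.

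Second, unadjusted change is the sum of a muscle part and a liver part. The muscle part may well fall: section 1.3.1 reports lower CK in treated *mdx* mice as evidence of benefit. A drug that works on muscle could therefore hold mean ALAT flat while a liver contribution grows. A reader of the study report who relied on the ALAT rows alone would be reassured without good reason, about an organ risk the protocol names.

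**Working it through.** The protocol gives no baseline enzyme multiples, variances or ALAT–CK relation, so it has no figure to reproduce. What follows illustrates size under stated assumptions.

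**1. The shift table.** Assume each reading equals the boy's true level times a log-normal error with log SD 0.3. Let b be the true baseline in multiples of ULN and f the true fold effect. Then

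P(normal to high) = Φ(ln(1/b)/0.3) × Φ(ln(b·f)/0.3).

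| True baseline (x ULN) | f = 1 | f = 2 | f = 3 |
|---|---|---|---|
| 0.5 | 1.0% | 49.5% | 90.2% |
| 1.5 | 8.0% | 8.8% | 8.8% |
| 3, 6 or 10 | 0.0% | 0.0% | 0.0% |

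Example, 0.5 x ULN with a doubling: Φ(ln 2/0.3) = 0.990, Φ(0) = 0.500, product 0.495. At 3 x ULN or more, high-to-high is 100% to the nearest tenth of a percent, with no effect, a doubling or a tripling. At 1.5 x ULN, no effect and a doubling differ by 0.8 percentage points. For a marker that starts normal, the same table works well.

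**2. Unadjusted change.** Let m be the muscle-source share of baseline ALAT and c the fractional fall in CK. If muscle-source ALAT falls in proportion to CK (assumption), it drops by m·c of baseline ALAT. Total ALAT then stays flat when the liver contribution rises by that amount.

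| CK fall c | m = 1 | m = 0.8 |
|---|---|---|
| 20% | 20% of baseline ALAT | 16% |
| 30% | 30% | 24% |
| 50% | 50% | 40% |

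**3. Unadjusted change is not blind.** Suppose ALAT truly doubles in a cohort of three boys and CK does not move. With within-boy log SD s, the standard error of the mean log change is s√2/√3. The chance that the mean exceeds 1.96 standard errors is Φ(ln 2/SE − 1.96). For s = 0.3, 0.4 and 0.6 the SE is 0.245, 0.327 and 0.490, and the chance is 0.81, 0.56 and 0.29. The protocol plans no test; the figures show only that a large rise would usually be visible when s is small. They say nothing of its source.

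**4. Own-baseline multiples.** Take the baseline as the geometric mean of three pre-treatment readings, again with log SD 0.3. The log ratio of a later reading to that baseline has SD 0.3 × √(1 + 1/3) = 0.346. The chance of exceeding twice baseline is Φ((ln f − ln 2)/0.346): 2.3% for f = 1, 50% for f = 2 and 87.9% for f = 3. This does not depend on how far above ULN the boy started. Twice baseline is only an example of a reporting category.

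**5. Limits of a CK ratio.** If ALAT follows CK with log-log slope β and the liver does nothing, ALAT/CK changes by the factor (1 − c)^(β − 1). With β = 1 it stays put. With β = 0.5, CK falls of 20%, 30% and 50% raise it by 12%, 20% and 41%. With β = 0 they raise it by 25%, 43% and 100%. The ratio can therefore rise without any liver injury.

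**The case against.** The strongest reply is that the hepatic read-out does not rest on ASAT, ALAT and LDH. Section 5.3.4.1 says bilirubin, gamma-GT and ALP are not affected by the disease (ALP may vary with age). They are in the Appendix 3 panel and pass through the same 8.5.5.4 tables; GLDH and direct bilirubin are in the extension's hepatic panel (5.6.5.1). CK is tabulated too, so falling CK beside flat ALAT would appear in nearby rows. The synopsis says all safety data will be listed and examined for signals, which is feasible with 12 to 18 boys. In the extension, the liver findings in 5.6.8.1 are serious adverse events under 7.1.2, and 8.5.5.4 tabulates those. All of this stands. A reader might infer that drug hepatotoxicity could not show at all; the documents do not support that.

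The premise also needs care. Section 5.6.5.1 says only that boys may have raised levels, and no baseline multiples are given. Exclusion criterion 11 removes values suggesting hepatic impairment, but it sets no ULN limit, so muscle-source elevation remains eligible.

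A further reply is that analysis detail is left to a statistical analysis plan that is not shown. That would answer silence. Here 8.5.5.4 states a method, and the method does not follow 5.3.4.1.

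The patient-level safeguards are partial. The CK regression is one optional step after a change has already been judged disproportionate, and the 5.6.8.1 criteria apply only beyond the study period. Neither gives a summary by dose group.

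**Conclusion.** The point holds as a mismatch between a stated summary and the protocol's own reading rule. For boys who start well above ULN, the normal-range shift table for ASAT, ALAT and LDH carries almost no information, and unadjusted change cannot separate muscle from liver. The possible offset is about 20%, 30% or 50% of baseline ALAT for CK falls of the same size. That assumes nearly all baseline ALAT comes from muscle and that this part moves in proportion to CK; the offset shrinks with the muscle share. The shift-table figures rest on the assumed baselines and log SD.

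Two stronger inferences should be resisted. The first reads CK falls of 20%, 30% and 50% as hiding liver-source rises of 25%, 43% and 100%. Those figures (1/0.8 − 1, 1/0.7 − 1, 1/0.5 − 1) are the excess of flat ALAT over its CK-proportional expectation, not liver contributions as a share of baseline. The second extends the criticism to serum creatinine. Section 5.6.5.1 says only that creatinine may vary with muscle mass, not that it starts above range.

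This is a moderate defect in descriptive reporting. It is worth correcting because the risk is named and the remedy uses existing data.

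**What to change.** Amend 8.5.5.4 so that it carries over the rule in 5.3.4.1:

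- **Own-baseline shifts.** Tabulate ASAT, ALAT and LDH in multiples of each boy's own pre-treatment baseline, in place of or beside the normal-range shift table. Visits 1, 1a and pre-dose visit 2 supply three values; state how they are combined (for example, the geometric mean) and set the reporting categories in advance.
- **CK-relative display.** Per visit and dose group, show change in log ASAT and log ALAT against the concurrent change in log CK, plotted or listed, with the log enzyme/CK ratio as a descriptive summary. Place it next to bilirubin, gamma-GT and, in the extension, GLDH.

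CK is measured in the same samples, so no visit or blood draw is added. The cost is analysis wording and a few tables or plots. The drawback is that the log ratio assumes proportionality with CK, so a CK fall alone can raise it. It should be read descriptively, with both components shown. These are reporting categories only; no dosing or stopping rule changes.

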#### **8.5.5.5      Pharmacodynamic analysis**

Endogenous production of the expected mRNA (assessed by RT-PCR on RNA isolated from muscle biopsy and mononuclear blood cells) will be reported by means of RT-PCR and gel electrophoresis analysis (photograph), including sequence analysis of the resulting products to confirm the precise exon 51 skipping.

The presence and localization of novel dystrophin protein (assessed by immunofluorescence analysis and western blot analysis) will be reported. No formal analyses will be performed for dystrophin presence and localization.

All other effect parameters will be reported using descriptive statistics (frequency, mean, standard deviation, median, minimum, and maximum). Changes from baseline measurements will be calculated and descriptive statistics will be computed.

#### **8.5.5.6      Pharmacokinetic analysis**

Plasma concentration vs. time profiles of PRO051 will be analyzed. Pharmacokinetic parameters AUC,  $C_{max}$ ,  $C_{trough}$ ,  $t_{max}$ , clearance, volume of distribution and elimination half-life will be obtained. Linearity of PRO051 pharmacokinetics will be evaluated using ANOVA on log-transformed, dose normalized PK parameters.

### **8.5.6      Study parameters**

#### **8.5.6.1      Effect parameters**

The following effect parameters will be assessed:

- Production of exon skip 51 mRNA (assessed by RT-PCR on RNA isolated from muscle biopsy and from mononuclear blood cells)
- Presence of dystrophin expression (assessed by immunofluorescence analysis of cross-sections derived from the muscle biopsy and by Western blot analysis of total protein extracts from the muscle biopsy)
- Muscle function (distance walked in 6 minutes and timed tests: 10-meter walk/run, rising from floor, stair climb)
- Muscle strength (QMT, MMT)

#### **8.5.6.2      Safety parameters**

The following safety parameters will be assessed:

- Frequency and number of adverse events
- Local tolerability
- Safety hematology and biochemistry parameters
- Coagulation (aPTT)
- Urinalysis
- Complement activation (complement split products C3a, SC5b-9, Bb)
- Inflammatory response (IL-6, TNF- $\alpha$ , MCP-1)
- Immune response to dystrophin (antibodies)
- ECG, heart rate and blood pressure

#### **8.5.6.3      Pharmacokinetic parameters**

The following pharmacokinetic parameters will be assessed:

- $t_{1/2}$
- AUC: 0-24h, 24h-7d, 0- $\infty$
- $C_{\max}$ ,  $C_{\text{trough } 7d}$
- $t_{\max}$
- distribution volume
- clearance

## 8.6 Study report

At the conclusion of the study period, after the data are analyzed, the sponsor will prepare an integrated study report. A draft copy of the report will be available for review by the principal investigators.

At the conclusion of the treatment beyond study period, after the data are analyzed, the sponsor will prepare an additional study report. A draft copy of the report will be available for review by the principal investigators.

## **9 Administrative procedures**

### **9.1 Basic principles**

The study will be performed in accordance with the International Conference on Harmonisation Good Clinical Practice (ICH-GCP) requirements, the Declaration of Helsinki (see Appendix 1), current FDA regulations and guidelines, the European Clinical Trials Directive and associated guidelines, as well as all other applicable national and local laws. Written informed consent will be obtained for this study by the principal investigator or his/her designee from all subjects prior to any study-specific procedures

### **9.2 Ethical considerations**

#### **9.2.1 Independent Ethics Committee/Institutional Review Board approval**

Written approval must be obtained from the IEC/IRB prior to release of clinical supplies and commencement of the study.

The protocol, the IB, IMPD, the subject information sheet, the consent form, the investigator's curriculum vitae and the advertisements (if any) will be submitted to the applicable Independent Ethics Committee (IEC) or Institutional Review Board (IRB). The IEC/IRB must be constituted and working in compliance with ICH-GCP.

A copy of the documented approval must be included in the Trial Master File.

Any (non) substantial amendment to the protocol or subject information and consent form will be submitted to the IEC/IRB of the investigational centre and written approval will be obtained for substantial amendments prior to implementation.

#### **9.2.2 Regulatory requirements**

The study will only start after authorization has been received from the relevant Competent Authorities.

#### **9.2.3 Insurance of the subject**

The sponsor will cover this study by means of an adequate insurance of the subject which will be in place prior to the start of the study. As evidence of this insurance, a copy of the Insurance statement will be provided to the investigator for storage in the Investigator File.

#### **9.2.4 Informed consent procedures**

It is the responsibility of the Investigator to obtain written Informed Consent from the subject. Information about the study will be given to the subject both verbally and in writing. The written subject information sheet will explain the objectives of the study, its potential risks and benefits. The investigator must be satisfied that the subject has understood the information provided before written consent is obtained.

It should be made clear that refusal to participate or withdrawal from the trial at any stage is without any prejudice to the subject's subsequent care. No subject should be obliged to participate in the trial. The subject must be given ample opportunity to enquire about details of the trial. If there is any doubt as to whether the subject has understood the written and verbal information, the subject should not enter the study.

The subject must be made aware that the monitors, auditors, the IEC/IRB and regulatory authorities will be granted direct access to the study subjects source medical records without violating subject confidentiality, and to the extent permitted by applicable regulations.

If the subject agrees to participate in the study he will be asked to sign and date a consent form which will be kept by the Investigator. The subject information leaflet and a copy of the signed informed consent will be provided to the subject.

The signed consent forms will be retained by the investigator and made available (for review only) to the study monitor and auditor on request.

### **9.2.5 Confidentiality of subject records**

Clinical research personnel assigned by the sponsor will require direct access to the subject's notes for source data verification. The confidentiality of all the subjects' identities will be maintained.

Only subjects' initials, date of birth and study number will be used on CRFs and in all study correspondence. No material bearing a subject's name will be kept on file by the sponsor or clinical research personnel assigned by the sponsor.

All information disclosed to the investigator by the sponsor or persons assigned by the sponsor shall be treated by the investigator as strictly confidential. The Investigator shall only use such information for the purpose of conducting the clinical trial described in this protocol and the investigator agrees not to disclose such information to any third party except those of his colleagues and employees who are assisting in the conduct of the study and who are bound by the obligations of confidentiality.

Information concerning the study drug, patent applications, processes, unpublished scientific data, the Investigator's Brochure and other pertinent information is confidential and remains the property of the sponsor. Details should be disclosed only to the persons involved in the approval or conduct of the study. The investigator may use this information for the purpose of the study only. It is understood by the investigator that the sponsor will use the information obtained during the clinical study in connection with the development of the drug and therefore may disclose it as required to other clinical investigators or to regulatory agencies. In order to allow for the use of the information derived from this clinical study, the investigator understands that he has an obligation to provide the sponsor with all data obtained during the study.

## **9.3 Financial disclosure**

In compliance with 21 CFR part 54, any listed or identified investigator or sub-investigator (including the spouse and any dependent children of said individuals) directly involved in the treatment or evaluation of research subjects will disclose the following information for the time period during which the investigator is participating in the study and for 1 year following completion of the study:

- Any financial arrangement entered into between the sponsor(s) and the investigator, whereby the value of the compensation to the investigator for conducting the study could be influenced by the outcome of the study;
- Any other significant payments totaling > € 5,000.00, exclusive of the costs of conducting this or other clinical studies, by the Sponsors such as a grant to fund ongoing research, compensation in the form of equipment, retainer for ongoing consultation, or honoraria;
- Any proprietary interest in the product being evaluated;
- Any significant equity interest, including ownership interest, stock options, or other financial interest whose value cannot be determined through reference to public prices or any equity interest in Prosensa Holding B.V. that exceeds € 5,000.00.

